### Interim analyses {21b}

An interim analysis is planned to assess both efficacy and futility, and a sample size re-estimation will be conducted once the 548th participants in the mITT analysis set complete the day 28 assessments. The IDMC, supported by an unblinded statistical centre, will regularly review safety data and evaluate the interim efficacy analysis.

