### Sample size {14}

This study aims to determine the efficacy of a new antiviral compared to placebo in reducing critical illness or all-cause mortality on day 28 in COVID-19 patients.

The sample size was calculated based on the superiority test. The primary endpoints are the disease critical rate and mortality rate. Based on the data reported in Hong Kong for patients with COVID-19 from the end of 2020 to March 2022, the number of deaths and serious illnesses was 6866 and 8875, respectively [21]. Previous data on another antiviral drug, Paxlovid, showed that the placebo group had 65 hospitalizations and 12 deaths, while the Paxlovid group had no deaths and 8 hospitalizations [5]. Combined with data from Hong Kong, it was speculated that there may be 15–16 severe patients in the placebo group and 2 severe patients in the Paxlovid group. Therefore, the disease critical rate and mortality rate in other countries and China are assumed to be 2.6% in the standard treatment group and can be reduced to 0.19% with effective treatment. With a power of 90% (1 sided *α* = 0.025 and *β* = 0.10), a sample size of 986 patients in each group is needed. The sample size calculations were performed using SAS software, version 9.4 (SAS Institute Inc., USA).

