### Recruitment {15}

To account for a 10% dropout rate, the sample size increased to 1096 participants (548 in the azvudine group and 548 in the control group). To enrol enough participants, we set up special screening staffs in the fever clinic and emergency department where COVID-19 patients often visit, and screening staffs distribute COVID-19 antigen to suspected fever patients to identify candidates. In order to complete such large amount patients’ selection as soon as possible, we selected 46 study sites localized in 17 different provinces in China Mainland; thus, we will obtain timely enrolment to the greatest extent possible.

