### Procedure for unblinding if needed {17b}

The Interactive Response Technology (IRT) system will be programmed with instructions to maintain blinding. For anticipated and unanticipated serious adverse events, emergency unblinding may be performed only if the investigator must know the treatment grouping information to proceed in the event of an emergency in the subject (e.g. requiring resuscitation). The safety of the participant will always be the primary consideration in making this decision. The reason for unblinding and the date it occurs must be documented in the source documentation and case report form (CRF). The study-specific IRT reference manual and investigational product manual will provide contact information and further details on how to use the IRT system.

Unless efficacy is demonstrated at an interim analysis, the study will be unblinded after the statisticians finalize the statistical plan and the audit report in the data plan and lock the database. Details of the unblinded sponsor staff supporting the independent data monitoring committee (IDMC) and the timing of unblinding will be outlined in the unblinding plan.

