## Statistical methods

### Statistical methods for primary and secondary outcomes {20a}

All data will be analysed using SAS software, version 9.4 (SAS Institute Inc., USA). A two-tailed *p* < 0.05 will be considered statistically significant in all statistical tests (except for the main efficacy indicators and other specified instructions).

The full analysis set (FAS), modified intention-to-treat set (mITT), per-protocol set (PPS), and safety set (SS) will be divided for analysis. FAS includes all eligible and randomized patients. PPS includes eligible patients with better compliance (80–120%), and completing necessary items of CRF.SS includes all patients enrolled in the study who have received at least one dose of medication and have at least one safety evaluation. Baseline characteristics analysis will be based on FAS, efficacy analysis will be based on FAS and PPS, and safety analysis will be based on SS. Unblinded patients will be excluded from PPS.

Continuous data will be summarized as the mean ± standard deviation, median, minimum, maximum, lower quartile, and upper quartile. Categorical data will be presented and summarized as frequencies and percentages in each category.

Between-group comparisons will be conducted by using paired *t*-tests or Wilcoxon rank tests for continuous data, chi-square tests or Fisher exact tests for categorical data, Wilcoxon rank tests or CMH tests for ranked data, and Kaplan‒Meier estimates for time-to-event data. The principles of intention-to-treat analysis will be used.

Efficacy analysis will be based on FAS and PPS. The primary efficacy endpoints are COVID-19-related critical illness and all-cause mortality within 28 days (whichever happens first), which will be analysed based on a time-to-event manner. Kaplan‒Meier method will be used to describe the incidence rates of the primary endpoint in each group separately at 28 days. Between-group comparisons will be performed by the log rank test. A Cox regression model will be used to estimate the hazard ratio and corresponding 95% confidence interval and adjust for potential covariates such as centres. Secondary efficacy endpoint analysis will be performed according to general statistical considerations. The specifics of these methods will be thoroughly outlined in the statistical analysis plan.

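### The interim analysis is tied to an mITT set that is not described and is not an efficacy set, PPS exclusions can depend on outcome, and two sections differ on who supports the IDMC unblinded

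*Protocol article*

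**What the plan says.** **Interim look.** Interim analyses {21b} plans a single interim analysis for efficacy and futility, and states that "a sample size re-estimation will be conducted once the 548th participants in the mITT analysis set complete the day 28 assessments". The same section has an unblinded statistical centre support the IDMC.

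**Analysis sets.** Statistical methods {20a} lists FAS, mITT, PPS and SS. It then describes FAS (eligible and randomised), PPS (compliance of 80 to 120% and the necessary CRF items) and SS (dosed, with a safety evaluation). It does not describe mITT. It assigns the sets as follows: "efficacy analysis will be based on FAS and PPS, and safety analysis will be based on SS", and repeats the FAS and PPS basis when it introduces the primary endpoint. One sentence commits the analysis to intention-to-treat principles. On PPS it adds: "Unblinded patients will be excluded from PPS".

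**Unblinding.** Procedure for unblinding {17b} allows emergency unblinding only where the investigator must know the allocation to deal with an emergency, with resuscitation as the example. It foresees an early efficacy conclusion ("Unless efficacy is demonstrated at an interim analysis, the study will be unblinded" only after the plan is final and the database locked). It also refers to an unblinding plan: "Details of the unblinded sponsor staff supporting the independent data monitoring committee (IDMC").

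**Alpha.** The only level given for the primary endpoint is in Sample size {14}: "With a power of 90% (1 sided *α* = 0.025 and *β* = 0.10), a sample size of 986 patients in each group is needed". Statistical methods {20a} exempts the main efficacy indicators from its general two-tailed 0.05 and leaves method specifics to the SAP.

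**The concern.** Three things are left open or in conflict.

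1. **Interim population.** The only interim decision on efficacy, futility and sample size is triggered by, and apparently made on, a set that the article does not describe and does not list for efficacy. The final test is on other sets. The interim result and the final result may then rest on different patients.

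2. **Deciding population.** If FAS and PPS disagree, the text does not say which carries the superiority claim. This matters because PPS membership can depend on the outcome. A patient who deteriorates is more likely to be unblinded in an emergency or to stop dosing early, and so to leave PPS together with the event. Comparing the remaining patients is no longer a comparison of randomised groups.

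3. **Access to unblinded data.** Sponsor staff who know comparative interim results around a sample size re-estimation are a possible source of operational bias. The text leaves open whether they would know them.

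**Working it through.** **Planned size, to fix the scale.** Inputs from Sample size {14}: rates "assumed to be 2.6% in the standard treatment group and can be reduced to 0.19% with effective treatment", one-sided 0.025, power 90%. With unpooled variance, n per arm = (1.960 + 1.282)² × [0.026 × 0.974 + 0.0019 × 0.9981] / (0.026 − 0.0019)² = 10.507 × 0.02722 / 0.000581 = 492.4, so 493 per arm and 986 in total. Then 986 / 0.9 = 1095.6, which gives the 1096 in Recruitment {15}, where the article writes: "To account for a 10% dropout rate, the sample size increased to 1096 participants (548 in the azvudine group and 548 in the control group". So 986 reproduces as the total, not as the size of each group.

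**Interim timing.** 548 is 548/1096 = 0.50 of those randomised, or 548/986 = 0.556 of the evaluable target. Which fraction applies depends on what mITT is.

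**Events at stake under the planning rates.**
- Interim, 274 per arm: 274 × 0.026 = 7.1 and 274 × 0.0019 = 0.5, total 7.6.
- End, 493 per arm: 12.8 + 0.9 = 13.8.
- End, 548 per arm: 14.2 + 1.0 = 15.3.

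One event removed from PPS is therefore 1/15.3 = 6.5% to 1/13.8 = 7.3% of the final total.

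**How PPS can select on outcome.**
- *Unblinding.* {17b} confines emergency unblinding to emergencies; {20a} drops every unblinded patient. The patients dropped by this route are those with serious events, which can include the primary endpoint.
- *Compliance.* The denominator is not stated. If it is the 7 planned once-daily doses, 5/7 = 71% fails and 6/7 = 86% passes. A patient whose event stops dosing after 5 or fewer doses then leaves PPS. Criteria for discontinuing {11b} includes worsening illness among its grounds for stopping the drug, when joined with poor expected benefit and the patient's unwillingness to continue.

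**Type I error over two looks, conditional on no adjustment.** Take Z1 and Z2 bivariate normal with correlation √t and cut-off 1.96 at both looks. P(Z1 > 1.96 or Z2 > 1.96) = 0.0416 at t = 0.50 and 0.0406 at t = 0.556. A simulated pooled z-test on proportions gave 4.2% (274 then 548 per arm) and 4.1% (274 then 493) at a null rate of 2.6%, and 3.7 to 3.8% at 1.4%.

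**Boundaries that hold 0.025 at t = 0.50 (one-sided, interim/final).**
- Lan-DeMets O'Brien-Fleming type: 0.0015/0.0245, total N about 1099.
- O'Brien-Fleming: 0.0026/0.0240, about 1103.
- Pocock: 0.0147/0.0147, about 1205.

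**Does a different interim set void a boundary?** For the 0.0015/0.0245 split, the overall error is 0.0260 at correlation 0, 0.0255 at 0.5 and 0.0250 at 0.707. The union bound, 0.0015 + 0.0245 = 0.0260, covers any pair of sets, provided each test is valid on its own set.

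**The case against.** The strongest reply is that an article condenses the full protocol. Boundaries, alpha spending and the hierarchy of analysis sets usually sit in the SAP, which {20a} points to. One-sided 0.025 may be the overall level. Nor does the match of 986 to a single-look formula show that the interim was ignored, since O'Brien-Fleming-type boundaries add under 1% to N. This stands. A reader might infer that the trial runs at 4.2% error, but no section says that 0.025 is applied unadjusted at each look.

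A reader might also infer that no group-sequential boundary can hold when the sets differ. The calculation above shows otherwise: the excess for the 0.0015/0.0245 split is at most about 0.001.

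On the sets, the intention-to-treat sentence favours FAS, and excluding non-compliant and unblinded patients is common in per-protocol sets. Both points are fair. They do not remove the outcome-dependent exclusions, because efficacy rests on FAS and PPS with no order stated. It would go too far to put a figure on lost PPS power: the documents do not say how many endpoint patients would be unblinded or stop dosing, and emergency unblinding is optional, not routine.

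On access, a statistical centre may do the analysis while designated sponsor staff give other support, with details in the unblinding plan. The text does not say that these staff see comparative efficacy data, nor whether the re-estimation is blinded. So the point is a conflict to reconcile, not a demonstrated breach.

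The mITT point is not answered by condensation. The article chose to describe its sets, left out the one that drives the interim, and twice gave FAS and PPS as the efficacy basis.

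**Conclusion.** The concern holds as a conflict between sections and a weakness in the PPS rules. {21b} and {20a} disagree on the interim population, and {17b} and {21b} differ on who supports the IDMC unblinded. {20a} does not say which efficacy set decides. Its unblinding exclusion can remove patients because of their outcome; its compliance exclusion can do so too if compliance is counted against all 7 doses, which is an assumption.

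The scale is about 14 to 15 events in all at the planning rates, so a few exclusions could change the PPS result materially. The number is unknown.

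The article does not show that alpha is inflated. The 4.1 to 4.2% figure applies only if the unseen SAP makes no adjustment at either look, so the levels need confirming rather than correcting. The changes should be made, but they are modest.

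**What to change.** 1. Use one set for the interim and final primary analyses: FAS, by assigned arm. Remove mITT or make it identical to FAS, and restate the 548 trigger in that set.
2. Name FAS as the sole basis of the superiority claim and PPS as supportive.
3. In PPS, state the compliance denominator, measure compliance only up to the earlier of day 7 or the first endpoint event, and do not exclude for unblinding at or after that event.
4. Restrict comparative unblinded interim data to the independent statistical centre and the IDMC it serves. Reconcile {17b} with {21b}, saying what any unblinded sponsor staff may see.
5. Confirm the interim and final significance levels, for example 0.0015 and 0.0245 one-sided.

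The cost is protocol and SAP wording. If that split is adopted at t = 0.50, the final level falls from 0.025 to about 0.0245 and the total for 90% power rises from 1096 to about 1099. The changes should be made before anyone examines unblinded data.

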### Methods for additional analyses (e.g. subgroup analyses) {20b}

No additional analyses will be performed.

### Methods in analysis to handle protocol nonadherence and any statistical methods to handle missing data {20c}

The primary endpoint is defined as time-to-event data, non-endpoint events will be defined as censoring events, and the censoring date will be set as the last follow-up date. No carry-forward or multiple imputations will be conducted for missing data.

Missing data of secondary endpoints or safety endpoints will not be imputed. Missing data due to intercurrent events will be imputed by a multiple imputation approach under a prespecified estimand.

### Plans to give access to the full protocol, participant-level data, and statistical code {31c}

The datasets used and/or analysed during the current study will be available from the corresponding author upon reasonable request.

## Oversight and monitoring

### Composition of the coordinating centre and trial steering committee {5d}

This study was initiated by PUMCH and involves multiple centres. There is no other coordinating centre. Investigators from PUMCH act as coordinating investigators responsible for liaising and coordinating with other hospitals involved in the trial to promote and monitor the progress of the trial, with the assistance of the Contract Research Organization and Site Management Organization. The trial steering committee consists of the PUMCH clinical research team. The study team meets weekly to assess progress and data analysis. Meetings with subcentre investigators are held as needed to oversee the progress of the trial and to provide advice on problems encountered in subcentre project implementation.

The roles and responsibilities are as follows: the coordinating centre (Universidade Federal de Ciências da Saúde de Porto Alegre) is responsible for overseeing the overall progress of the trial, ensuring adherence to protocols, and liaising with involved universities.

### Composition of the data monitoring committee, its role, and reporting structure {21a}

The Data and Safety Monitoring Board (DSMB) of this clinical trial was established on June 18, 2023. The primary responsibility of the DSMB is to provide an independent review and evaluation of safety data in accordance with the protocol. It is responsible for reviewing safety results in a blinded or unblinded fashion, assessing adverse events collected in the study, evaluating cumulative SAE reports, and, based on the results of the cumulative analysis of the data obtained, providing recommendations to the sponsor regarding trial execution and study adjustments to further safeguard the interests and safety of the subjects and to ensure that these potential risks are controlled in a timely and effective manner. The DSMB consists of five people, including the DSMB chairperson, members, and secretary, who are independent of the sponsor and competing interests. DSMB members and statisticians who analyse the writing of the submitted analyses will monitor unblinded and/or subgrouped safety data, discuss results, and formulate and vote on recommendations for the study. Participating unblinded statisticians will provide guidance and answer statistical questions. The secretary of the DSMB will retrieve the analysis report and maintain it as a confidential document.

### Adverse event reporting and harms {22}

All AEs, including SAEs, which will be coded according to the definition of severe adverse events published by the FDA, will be carefully assessed for their severity, degree, and potential causality with the intervention or other possible treatments. Once an SAE occurs, the study will be terminated. SAEs will be reported to the institutional academic and ethics committee within 24 h and be managed by the attending physician according to standard medical practice, and we will continue to follow up with the patient until the symptoms resolve or the treatment is discontinued. The project will cover the cost of any adverse reactions related to the use of azvudine.

### Frequency and plans for auditing trial conduct {23}

The monitor will review the trial conduct monthly, including checking the original data of participants and counting the biological samples. The process will be independent of the researchers and the sponsor.

### Plans for communicating important protocol amendments to relevant parties (e.g. trial participants, ethical committees) {25}

In the event of any proposed changes to the protocol, these changes will be thoroughly documented in protocol amendments. These amendments will be submitted for approval to the ethics committee and regulatory agencies before implementation.

### Dissemination plans {31a}

The trial data will be publicly available for publication in international peer-reviewed journals, regardless of whether the results are positive or negative.

## Discussion

This is a double-blind, randomized, placebo-controlled, superiority, phase III clinical trial designed to evaluate the efficacy of azvudine in preventing mild-to-moderate COVID-19 patients who have the potential to develop severe COVID-19 from progressing to critical illness and death.

Since the beginning of the COVID-19 pandemic in 2019, it has afflicted at least 700 million people worldwide, and nearly 7 million human deaths have been caused by COVID-19 (http://covid19.who.int) [1]. Although evidence shows that the pulmonary pathogenicity of the variant Omicron strain has significantly weakened, the severity and mortality rates of elderly patients and those with underlying diseases are still high [23, 24]. SARS-CoV-2 will coexist with humans for a long time, and patients with underlying diseases still face a high risk of severe COVID-19 and death [25].

The WHO and China both have issued diagnosis and treatment guidelines for COVID-19 infection, in which antiviral treatment including Paxlovid, molnupiravir, and remdesivir targeting COVID-19 is the cornerstone [3, 4]. However, antiviral drugs such as Paxlovid are not suitable for some patients due to complicated drug interactions [26]. In addition, the high cost limits the wide use of such drugs in developing countries. Therefore, affordable, safe, and effective antivirals are in great demand.

RNA synthesis is an essential step in the replication lifecycle of coronaviruses and typically uses natural nucleosides from host cells as substrates for successful replication [27]. Nucleoside and nucleotide analogue inhibitors are synthetic molecules similar to purines and pyrimidines that may be mistakenly incorporated during virus replication, thereby terminating the synthesis of viral RNA chains or causing mutations that result in loss of viral viability or preventing viral replication and transmission [28, 29]. Nucleoside analogues have been successfully used to treat viral DNA and RNA infections, such as HIV, hepatitis B virus, and several respiratory viruses, such as influenza [30–34]. Azvudine, as a nucleoside analogue, has been developed for the treatment of HIV, and its clinical safety and effectiveness have been proven in HIV-positive patients [35].

Preliminary prospective studies regarding the treatment of azvudine in COVID-19 were carried out, and data on efficacy and safety were collected. For instance, a pilot randomized, open-label, controlled study accomplished in 2020 found that azvudine may shorten the time to nucleic acid-negative conversion in 10 patients with mild COVID-19 [36]. Another randomized clinical trial (RCT) was performed to evaluate the efficacy of azvudine for patients with mild COVID-19, which confirmed that azvudine was effective in reducing the viral load [20]. However, these RCT studies were small and did not report the efficacy of azvudine on mortality in COVID-19 patients.

Several single-centre retrospective studies reported the rate of disease progression and mortality after azvudine treatment in COVID-19 patients. They matched the demographics and disease severity of patients with COVID-19 through propensity score analysis and found that azvudine reduced the rate of disease progression, as well as the rate of COVID‐19‐related hospitalization. A retrospective study of mild-to-moderate COVID-19 patients showed that azvudine reduced the rate of disease progression and the hospitalization rate. Another study also showed that azvudine reduced the risk of disease progression in COVID-19 patients with preexisting conditions [37, 38]. However, inconsistent results are found among different studies regarding the impact of azvudine on all-cause mortality [17, 37–39]. Nonetheless, there are promising results showing that there was no difference in mortality between COVID-19 patients using Paxlovid and those using azvudine, which was a consistent finding in two retrospective cohort studies [40, 41].

In general, patients have a good tolerance to azvudine, and this drug may reduce the risk of critical illness and death in patients who are at risk of potentially progressing to critical COVID-19 infection.

As a new small-molecule antiviral drug, azvudine has the advantages of low price and less drug interactions compared with Paxlovid, an anti-COVID-19 drug used worldwide. However, due to insufficient research data, there is currently no multicentre, randomized clinical trial to prove the efficacy of this drug based on the endpoints of severe illness and death. The published research on the prospective cohort study of azvudine is limited to the impact on viral load, while research data support is still lacking for its impact on the critical disease rate and mortality of COVID-19, which clinicians truly care about.

In conclusion, a well-designed, randomized double-blind placebo-controlled study to assess the efficacy of azvudine in symptomatic adult COVID-19 participants who are at increased risk of progressing to critical illness is urgently needed. Our study will attempt to evaluate the difference in efficacy between azvudine antiviral treatment and placebo and to answer the important clinical question of the impact of azvudine on the critical illness rate and mortality of COVID-19.

